## Abstract

**Background:**

Juvenile dermatomyositis (JDM) is a rare, often chronic, systemic autoimmune disease of childhood, characterized by inflammation of the microvasculature of the skeletal muscle and skin. Prominent clinical features include significant exercise intolerance, muscle weakness, and fatigue. Despite pharmacological improvements, these clinical features continue to affect patients with JDM, even when the disease is in remission. Exercise training is increasingly utilized as a non-pharmacological intervention in the clinical management of (adult) patients with chronic inflammatory conditions; however no randomized controlled trials (RCT) have been performed in JDM. In the current study, the efficacy and feasibility of an exercise training program in patients with JDM will be examined.

**Methods/design:**

Subjects (*n* = 30) will include 8–18 year olds diagnosed with JDM. The intervention consists of an individually tailored 12-weeks home-based exercise training program in which interval training on a treadmill is alternated with strength training during each session. The program is based on previous literature and designed with a defined frequency, intensity, time, and type of exercise (FITT principles). Primary outcome measures include aerobic exercise capacity, isometric muscle strength, and perception of fatigue. The study methodology has been conceived according to the standards of the CONSORT guidelines. The current study will be a multi-center (4 Dutch University Medical Centers) RCT, with the control group also entering the training arm directly after completion of the initial protocol. Randomization is stratified according to age and gender.

**Discussion:**

The current study will provide evidence on the efficacy and feasibility of an individually tailored 12-week home-based exercise training program in youth with JDM.

**Trial registration:**

Medical Ethics Committee of the University Medical Center Utrecht, the Netherlands: 11–336; Netherlands Trial Register (NTR): NTR 3184.

## Background

The pediatric forms of inflammatory idiopathic myopathies (IIM) embody a group of rare systemic autoimmune conditions, characterized by chronic skeletal muscle inflammation with an age of onset of <18 years. Despite being a rare condition, juvenile dermatomyositis (JDM) is the most common type of pediatric IIM, representing about 85% of IIM diagnoses in childhood [1]. JDM is characterized by inflammation of the microvasculature of the skeletal muscle and skin. While the etiology of the disease remains largely unknown, environmental and genetic factors are thought to play a role in its development [2]. Prominent clinical features are significant muscle weakness [3], anaerobic- and aerobic exercise intolerance [4-8], and fatigue [9]. Furthermore, the patients show a skin rash commonly seen on the face and extremities [10]. Less frequently, the gastrointestinal tract, lungs, heart, and rarely the central nervous system may also be involved [10-12]. Despite pharmacological improvements, these clinical features are persistently experienced in patients with JDM, even when the disease is in remission [12-14].

Exercise training is increasingly utilized as a non-pharmacological intervention in the clinical management of patients with chronic inflammatory conditions. As opposed to typically developing healthy children, those with chronic illness are often restricted in their participation in physical activity as a consequence of real or perceived limitations imposed by their condition. The chronic condition itself often causes hypoactivity leading to a deconditioning effect and a reduction in functional ability, which ultimately results in a downward spiral of further hypoactivity and deteriorating health [15]. Further, children who are hypoactive are also thought to be at high risk of developing a number of secondary health complications commonly associated with a sedentary lifestyle including cardiovascular disease, obesity, and pre-diabetes [15]. Exercise training might prevent or slow down the deconditioning as a result of hypoactivity, but it might also reduce the systemic inflammation. To date, very little is known about the effects of exercise training in chronic pediatric conditions, including JDM. In fact, only one study has examined the effect of exercise training in one child with JDM in remission. Omori et al. reported improvements in muscle strength, aerobic exercise capacity, and muscle function in this child after completing a 16-week exercise training program [16]. In adults with active as well as inactive stable dermatomyositis, exercise training has been shown to improve aerobic exercise capacity, muscle strength, functional ability, fatigue, and health status [17]. These improvements may theoretically be explained by the role of chronic exercise in inducing changes at the origins of the observed exercise intolerance, which include decreased capillary density, perivascular atrophy of type I and II muscle fibers, and reduction of key enzymes essential for producing ATP [18].

Studies in patients with adult and juvenile dermatomyositis suggest that exercise training is safe since it has not been associated with any increases in the degree of inflammation after a single bout of exercise in JDM [19], or after an exercise training program in one patient with JDM [16], as well as in a number of adult patients with dermatomyositis [17].

While there is limited evidence to support the role of exercise training in the management of patients with JDM, definitive evidence is still lacking. In fact, to our knowledge, no randomized controlled trials (RCT) of exercise training in JDM have been performed, which may be secondary to limited patient availability and other feasibility issues.

As such, we designed a RCT to study the feasibility of an individually tailored 12-week home-based exercise training program, and to assess its efficacy in children and adolescents with JDM. The wash-out effects of this program after another 12 weeks will also be examined.

## Methods/design

### Study design

The current study is a multi-center (4 sites) randomized controlled trial, with the control group also entering the training arm directly following completion of the initial protocol. After randomization (1:1), subjects in both groups will perform a test battery of exercise tests, questionnaires, and other measurements (see study outcomes) (T0 measurement). Thereafter, subjects in the intervention group will receive an exercise training regimen, while the subjects in the control group will continue to receive standard care over a 12-week period. Subsequently, subjects in both groups will repeat the battery of tests from T0 (T1 measurement). Subjects in the intervention group will then receive individual advice based on their T1 results and educated on the physical activity guidelines for children [20] in order to help maintain fitness levels following the intervention. Subjects in the control group will enroll in the exercise training program. Following this 12-week period, subjects in both groups will repeat the battery of tests from T0 and T1 (T2 measurement) and the subjects in the control group will receive individual feedback in the same manner as the intervention group at T1. After 12 weeks, the subjects in the control group will repeat the battery of tests from T0, T1, and T2 (T3 measurement). See Figure1 for a flow diagram of the study design.

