### Randomization and blinding

Included subjects will be stratified according to age (≤ or >12 years) and gender after which they will be randomized to either the intervention or the control group. The randomization process will be performed by a person with no clinical involvement in the trial. Blocking is used to ensure close balance of the numbers in each group at any time during the trial. Randomly varying the block size (2 or 4) reserves the unpredictability of the sequence. The sequences will be concealed until interventions are assigned. The researchers performing the assessments, as well as those charged with data analyzes will be blinded to treatment allocation.

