### Study outcomes

#### Efficacy

The primary and secondary efficacy outcome measures along with the tools for these assessments are described below and in Table2.

**Table 2 T2:** The primary and secondary study outcomes and the accompanying measurement tools used

	**Items**	**Range**	**+/−**
**Aerobic exercise capacity***(Maximal exercise test on treadmill)*			
VO_2peak_ [l·min^-1^]	na	>0	+
VO_2peak/kg_ [ml·kg^-1^·min^-1^] ^1^	na	>0	+
O_2_ pulse [ml·beat^-1^]	na	>0	+
Endurance time [min]	na	>0	+
VO_2VAT_ [l·min^-1^]	na	>0	+
VO_2VAT/kg_ [ml·kg^-1^·min^-1^]	na	>0	+
**Isometric muscle strength***(Hand-held dynamometry – Break method)*			
Maximal force right knee extensors [N]	na	>0	+
Maximal force left knee extensors [N]	na	>0	+
Maximal force right hip flexors [N]	na	>0	+
Maximal force left hip flexors [N]	na	>0	+
**Perception of fatigue***(PedsQL Multidimensional Fatigue Scale – patient form)*			
Total score	18	0-100	+
Subscale *General Fatigue* score	6	0-100	+
Subscale *Sleep/Rest Fatigue* score	6	0-100	+
Subscale *Cognitive Fatigue* score	6	0-100	+
**Muscle soreness***(10-cm Visual Analogue Scale muscle soreness)*			
Visual Analogue Scale muscle soreness [cm]	na	0-10	-
**Muscle function***(BOT-2 Subscale 8 – Strength)*			
Total score	5	0-42	+
Item *Distance standing long jump* [m]	na	>0	+
Item *Amount of sit-ups in 30 s*	na	≥0	+
Item *Amount of push-ups in 30 s*	na	≥0	+
Item *Time wall sit* [s]	na	0-60	+
Item *Time V-up* [s]	na	0-60	+
**Muscle function***(Childhood Myositis Assessment Scale)*			
Total score	14	0-52	+
**Functional sub maximal aerobic exercise capacity***(6-Minute Walk Test)*			
Distance [m]	na	>0	+
**Physical activity enjoyment***(Physical Activity Enjoyment Scale)*			
Total score	17	17-119	+
**Quality of life***(PedsQL Generic Core Scale – patient form)*			
Total score	23	0-100	+
Subscale *Physical Functioning* score	8	0-100	+
Subscale *Emotional Functioning* score	5	0-100	+
Subscale *Social Functional* score	5	0-100	+
Subscale *School Functioning* score	5	0-100	+
**Functional ability***(Childhood Health Assessment Questionnaire 30 + 8)*			
Subscale *Dressing* score	4	0-3	-
Subscale *Arising* score	2	0-3	-
Subscale *Eating* score	3	0-3	-
Subscale *Walking* score	2	0-3	-
Subscale *Hygiene* score	5	0-3	-
Subscale *Reach* score	4	0-3	-
Subscale *Grip* score	5	0-3	-
Subscale *Activities* score	5	0-3	-
Subscale *School/Extracurricular* score	8	0-3	-
Disability score [%]	38	0-100	-
Visual Analogue Scale pain [cm]	na	0-10	-

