### Primary study outcomes

*Aerobic exercise capacity* will be measured with a treadmill-based (RAM, Accuramed BVBA, Lummen, Belgium) incremental maximal exercise test according the protocol set out by the German Society for Pediatric Cardiology [33]. Briefly, the test starts at a speed of 2 km·h^-1^ with a 0% grade; the speed increases by 0.5 km·h^-1^ and the grade by 3%, up to a maximum of 21%, every 90 s. The test is terminated upon voluntary exhaustion, despite strong verbal encouragement.

Throughout the test, the subject will wear a facemask (Hans Rudolph Inc, Kansas City, MO) connected to a gas analysis system (ZAN 600, Accuramed BVBA, Lummen, Belgium), which will allow for a sample of expired gases to pass to a flowmeter, an oxygen analyzer, and a carbon dioxide analyzer. Volume calibration and gas analysis calibration will be performed before each testing session. The flow meter and gas analyzers are connected to a computer that calculate breath-by-breath minute ventilation (VE), oxygen uptake (VO_2_), carbon dioxide output (VCO_2_), and the respiratory exchange ratio (RER = VCO_2_/VO_2_) using conventional equations. HR will be measured continuously via a 12-lead electrocardiogram (CardioPerfect, IT medical, the Netherlands). The test will be deemed maximal when the HR is >180 beats·min^-1^ and/or the RER >1.0.

The outcome measures related to aerobic exercise capacity that will be assessed include: VO_2peak_ [l·min^-1^]: the average volume of the absolute oxygen uptake during the last 30-s period of the test; VO_2peak/kg_ [ml·kg^-1^·min^-1^]: the absolute VO_2peak_ divided by body mass. This variable was used for the power calculation; VO_2VAT_ [l·min^-1^]: the absolute VO_2_ eliciting the ventilatory anaerobic threshold (VAT). The VAT will be determined as defined by an increase in both the ventilatory equivalent of oxygen (=VE/VO_2_) and end-tidal pressure of oxygen with no concurrent increase in the ventilatory equivalent of carbon dioxide (=VE/VCO_2_); VO_2VAT/kg_ [ml·kg^-1^·min^-1^]: the absolute VO_2VAT_ divided by body mass; O_2_ pulse [ml·beat^-1^]; and endurance time [min]: the time from the start to the end of the protocol.

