*Isometric muscle strength* of the proximal muscle groups in the lower extremities will be measured on both the right and left sides with a calibrated CITEC hand-held dynamometer (C.I.T. Technics, Groningen, the Netherlands). Both the extensors of the knee joint and the flexors of the hip joint will be assessed with 3 consecutive measurements according to the ‘break method’, wherein the examiner gradually overcomes the muscle force and stops at the moment the extremity gives way [34]. The highest value of the 3 repetitions will be recorded. All within-subject tests will be performed by the same assessor using the same hand-held dynamometer to prevent inter-observer and inter-instrument bias [34].

*Perception of fatigue* will be measured with the Dutch translated PedsQL Multidimensional Fatigue Scale. This scale, designed to measure fatigue in pediatric patients, reflects 3 subscales: general fatigue, sleep/rest fatigue, and cognitive fatigue [35-37].

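### The T0 battery is scheduled after randomisation, and nothing in the text keeps allocation from children and parents until it is complete

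*Protocol article*

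**What the plan says.** Study design in the protocol article fixes the order of events: "After randomization (1:1), subjects in both groups will perform a test battery of exercise tests, questionnaires, and other measurements". This is the T0 measurement. Training or usual care follows it, and for controls "while the subjects in the control group will continue to receive standard care over a 12-week period".

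Randomization and blinding covers two groups of staff: "The researchers performing the assessments, as well as those charged with data analyzes will be blinded to treatment allocation". On concealment it says: "The sequences will be concealed until interventions are assigned". Children and parents are not listed as blinded, and the time at which they are told their group is not given.

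All three primary domains rely on the child's effort or report:
- Treadmill test (Primary study outcomes): "The test is terminated upon voluntary exhaustion, despite strong verbal encouragement". The check on effort is: "The test will be deemed maximal when the HR is >180 beats·min^-1^ and/or the RER >1.0".
- Hand-held dynamometry by the break method (same section), "wherein the examiner gradually overcomes the muscle force and stops at the moment the extremity gives way".
- Fatigue (Table 2), by the "PedsQL Multidimensional Fatigue Scale – patient form".

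**The concern.** Home treadmill training against usual care cannot be masked from a family once the group is known. If a child knows at T0 that training starts now, or only in 12 weeks, that knowledge may change how hard the child runs or pushes, or how tired the child reports being. T0 would then no longer be a value untouched by allocation, and the two arms could differ at T0 for a reason other than chance.

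T0 is used in several places:
- the comparison of the groups at T0 (Baseline description of groups; Intervention group Vs control group);
- the control group's T0–T1 change, set against its T1–T2 change (Intervention in control group);
- the intervention group's pre-intervention value in the wash-out analysis;
- the peak heart rate that defines training intensity in the intervention arm (Intensity – interval training on treadmill).

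A baseline altered in this way cannot be repaired later by analysis, because the size of the alteration is not observed.

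**Working it through.** **Order and protection.** Study design states that T0 follows randomisation; this is not a detail lost in condensing. Randomization and blinding protects assessors and analysts. Neither section says that families stay uninformed through T0, or that they are informed before it. The text therefore allows disclosure before T0 but does not show it.

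**Which estimates a T0 shift reaches.** Let b be the shift in mean T0 of the intervention arm relative to control caused by knowing the allocation, and τ the true effect at T1. Assume that T1 is not affected by the T0 shift.

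- T1 contrast: T1(I) − T1(C) = τ. Bias 0.
- Change-score contrast: [T1(I) − T0(I)] − [T1(C) − T0(C)] = τ − b. Bias b in size.
- T0-adjusted contrast with slope ρ: τ − ρb. Bias ρb in size.
- Control group's paired test: (T2 − T1) − (T1 − T0) = T2 − 2T1 + T0. A shift in the controls' own T0 enters in full.
- Wash-out against pre-intervention, intervention group: T2 − T0. A shift in that arm's T0 enters in full. For controls the pre-intervention value is T1, so T0 plays no part.

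If b is negative (intervention arm lower at T0), change and adjusted estimates are inflated. If b is positive, they are diluted. The documents give no ground for choosing.

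**Illustrative size.** Inputs from Power calculation: mean 33, SD 8 ml/kg/min, improvement of 22%, 11 evaluable per group. Target = 0.22 × 33 = 7.26 ml/kg/min. Inputs that are assumptions, with no source in the documents: a shift of 3–5% and a slope (equal to the T0–T1 correlation) of 0.7.

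- Shift: 0.03 × 33 = 0.99; 0.05 × 33 = 1.65 (1.0–1.7 ml/kg/min).
- Change score: 0.99 / 7.26 = 14%; 1.65 / 7.26 = 23%.
- T0-adjusted: 0.7 × 0.99 = 0.69 and 0.7 × 1.65 = 1.16; divided by 7.26, 10% and 16%.

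**Against sampling error.** With 11 per arm, SD 8 and ρ = 0.7, the adjusted SE is 8 × √(1 − 0.49) × √(2/11) = 2.4, so a bias of 0.69–1.16 is about 0.3–0.5 SE. The change-score SE is 8 × √(2 × 0.3) × √(2/11) = 2.6. Two-sided type I error (normal approximation, nominal 0.05) for assumed shifts:

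| Shift b (ml/kg/min) | Change score | T0-adjusted |
|---|---|---|
| 1 | 0.07 | 0.06 |
| 2 | 0.12 | 0.09 |
| 3 | 0.21 | 0.14 |

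At b = 2, letting ρ run from 0.5 to 0.9 gives 0.09–0.26 (change score) and 0.06–0.23 (adjusted).

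No figure stated in the plan depends on this point, and moving T0 does not change the sample size.

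**The case against.** The strongest reply is that the article gives a sequence, not a time of disclosure. Training or usual care begins only after T0, and the statement on concealment fits a list drawn first and opened to families after T0. The flow diagram is not shown, and the full protocol may settle the matter. This stands: a reader might infer that children know their group at T0, but the text does not say so.

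A reader might also call the trial unblinded. It is open to children and parents only. Blinded assessors give the encouragement and perform the break test, which limits differential coaching and examiner bias. The HR/RER rule adds a check on treadmill effort. These safeguards are real but partial: they do not control the child's own effort or answers, the rule is met by either criterion alone, and strength and fatigue have no such check.

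It is tempting to read the percentages above as bias in the main result. The section on intervention versus control names group as the independent variable and compares the arms at T0 and at T1; it names neither change scores nor T0 adjustment. A pure T1 contrast has no bias from a T0 shift.

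Finally, one might argue that the present order damages the intention-to-treat set through withdrawals before T0. A child who leaves on learning the allocation lacks T1 under either order, so reordering does not supply the missing outcome. Nor does it remove the effect of knowing one's group at T1.

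**Conclusion.** The point holds as a weakness in a stated order of events. T0 follows randomisation, children and parents are not said to be uninformed, and the primary outcomes depend on effort or self-report. Influence on T0 is possible, not shown, and its direction is unknown.

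If the assumed 3–5% shift occurred, it would bias a change-score estimate by 14–23% of the 7.26 ml/kg/min target, or a T0-adjusted one by 10–16% at slope 0.7. These figures are illustrations resting on assumptions and do not apply to a T1-only contrast. The uses that remain exposed are the T0 group comparison, the control group's paired test, the intervention arm's wash-out comparison with pre-intervention, and its T0 peak heart rate. The documents do not support the stronger conclusion that the randomised comparison is biased. The case for acting is that the protection costs little and an affected baseline cannot be corrected afterwards.

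**What to change.** State the order as consent, then the complete T0 battery, then stratified randomisation and disclosure. If the list has to be drawn earlier, add a sentence that allocation is not disclosed to the child, parents or assessors until T0 is complete. Complete should include the seven-day activity monitoring where it forms part of T0, since that is free-living behaviour which knowledge of the group could also change. If allocation is already withheld in practice, saying so is enough.

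The cost is a minor change in scheduling: randomisation or disclosure waits until the battery is finished. The sample size does not change.

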**Figure 1 F1:**
[figure not shown]
Flow diagram of the study design.

### Subjects

All patients diagnosed with JDM by a pediatric rheumatologist/immunologist according to the Bohan and Peter criteria between the ages of 8 and 18 years from 4 outpatient clinics in the Netherlands will be assessed for eligibility. The 4 outpatient clinics include the Wilhelmina Children’s Hospital University Medical Center (UMC) in Utrecht, the Beatrix Children’s Hospital UMC in Groningen, the Sophia Children’s Hospital Erasmus Medical Center in Rotterdam, and the St. Radboud Children’s Hospital UMC in Nijmegen.

Patients will be excluded for eligibility upon (1) a medical status that contraindicates any form of exercise testing; (2) an insufficient understanding of the Dutch language in the patient and/or the parents/caregivers; (3) the presence of medical events that might intervene with the outcome of testing and/or the trial (such as a planned operation) and/or (4) a negative advise from the rheumatologist and/or physiotherapist based on resent relapse or no limitations in exercise tolerance (in other words: the patient was either not good enough or too good). All eligible patients will be asked to participate in the study. All parents/caregivers as well as subjects >12 years of age years must provide informed consent before enrolment in this study, which is approved by the Medical Ethics Committee of the UMC Utrecht, the Netherlands.

The flow of the subjects in the study will be depicted in the CONSORT Flowchart format [21]. The reasons for non-eligibility, declination to participate, and non-completion of the study will be reported in this flowchart as well.

### Exercise training program

The intervention comprises of an individually tailored 12-week home-based exercise training program, combining interval training on the treadmill (DKN Technology, T210, Belgium) with strength training. Both types of training are selected based on recommendations for patients with chronic conditions [22], as well as to specifically target the impaired exercise capacity and muscle strength observed in patients with JDM. The home-based nature of the intervention is selected to minimize the burden and costs associated with travel for both the patients and their parents. The training program is divided in 3 phases of 4 weeks each as shown in Table1. Concerning the FITT factors (frequency, intensity, time, and type) [23] and additional parameters, the following selections are made.

**Table 1 T1:** Description of the exercise training program

**Phase**	**1**	**2**	**3**
*Aim*	- Familiarizing the patient with the treadmill	- Improving aerobic exercise capacity	- Improving aerobic exercise as in phase 2 albeit with a higher intensity
	- Improving aerobic exercise capacity	- Improving muscle strength	- Improving muscle strength as in phase 2
	- Developing proper strength training techniques		
*Frequency [week*^*-1*^*]*	3	3	2
*Time/session [minutes]*	40-60	45-60	50-60
*Type*	Light interval training on treadmill and strength training.	Moderate interval training on treadmill and strength training.	Vigorous interval training on treadmill and strength training.
